#### Analysis

Continuous variables will be analysed by fitting linear mixed models, controlling for recruitment centre and baseline values as required. The proportion of participants who attend for at least 70% of the program will be compared between groups using a chi-squared test and the relative risk of non-completion will be determined. All data will be analysed by intention-to-treat. A per-protocol analysis will also be conducted to reduce the risk of Type 1 error, as recommended in the CONSORT Extension for reporting of non-inferiority and equivalence trials [61]. Alpha will be set at 0.05.

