### Recruitment and randomisation

Participants will be randomly allocated (1:1) to traditional centre-based pulmonary rehabilitation or telerehabilitation. A computer-generated, block randomisation scheme will be used with stratification for (i) recruitment in stable state vs post hospitalisation for respiratory exacerbation; (ii) site of recruitment; and (iii) diagnosis of ILD vs other diagnoses. Sequence generation will be performed by an individual who is independent of the research team and randomisation will occur using an online database. The randomisation sequence will be concealed from investigators. Participants will be allocated to groups after completion of baseline assessment. Given the nature of the intervention (exercise training) participants will not be blinded to the intervention, however all outcomes will be measured by an independent assessor blind to group allocation. The flow of participants through the study will be reported according to the recommendations of the Consolidated Standard of Reporting Trials (CONSORT) [32].

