##### Primary outcome

The Chronic Respiratory Disease Questionnaire (CRQ) is a disease specific measure of HRQoL for people with chronic respiratory disease [39]. The CRQ scores the domains of dyspnea, fatigue, mastery and emotional function. The primary outcome will be change in CRQ dyspnea domain (CRQ-D) from baseline to end intervention. The CRQ-D is a valid measure of HRQoL and is responsive to change with pulmonary rehabilitation in people with chronic respiratory diseases including COPD [40], bronchiectasis [41] and ILD [42].

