### Statistical analysis

#### Sample size

If there is truly no difference in the change in the dyspnea domain of the CRQ between telerehabilitation or traditional centre-based pulmonary rehabilitation at the end of the 8 week intervention, then 128 participants (64 in each group) are required to be 80% sure that the 95% confidence interval will exclude a difference in means of 2.5 points or more. This is the minimal important difference (MID) for the CRQ-D [56] and assumes a standard deviation of the change in CRQ-D of 4.8 points [57]. A total of 142 participants will be randomised to allow for 10% attrition. It is anticipated that recruitment will be evenly distributed across sites.

This sample size will also give sufficient power for secondary outcomes:*6-min walk distance (6MWD)*: if there is truly no difference in 6MWD at the completion of 8-weeks of centre-based pulmonary rehabilitation or telerehabilitation, a total of 108 participants will be required to ensure that the 95% confidence interval excludes a difference in group means of 30 m or more [43], assuming a standard deviation of change in 6MWD of 53 m [58].*Endurance Cycle Time****:*** if there is truly no difference between telerehabilitation and centre-based pulmonary rehabilitation in change in constant work rate endurance time on cycle ergometer, then 52 participants are required to be 80% sure that the 95% confidence interval will exclude a difference in means of 150 s or more. This is the MID for endurance time for patients with COPD [59] and assumes a standard deviation of 184 s [59].*Pulmonary rehabilitation adherence (program completion):* data from our centres indicate that only 65% people who are referred to pulmonary rehabilitation take up the referral and complete the program. Previous studies have documented completion rates for telerehabilitation programs of over 90% [23, 60]. Using a conservative estimate of 85% completion, 128 patients will be required to detect a difference in completion rates between telerehabilitation and traditional pulmonary rehabilitation.

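### The model for continuous outcomes names one of the three stratification factors and leaves covariate adjustment conditional, so the primary equivalence analysis is not fixed and may give up a little power

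*Protocol article*

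**What the plan says.** The Recruitment and randomisation section of the protocol article sets out block randomisation and describes its strata as follows: "stratification for (i) recruitment in stable state vs post hospitalisation for respiratory exacerbation; (ii) site of recruitment; and (iii) diagnosis of ILD vs other diagnoses". Allocation follows the baseline assessment, so all three factors and the baseline score are known before a participant is assigned.

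The Analysis section gives one sentence on the model for every continuous outcome: "Continuous variables will be analysed by fitting linear mixed models, controlling for recruitment centre and baseline values as required". It names site (as recruitment centre) and baseline. It does not mention recruitment state or ILD. The closing qualifier can be read as covering baseline only, or centre and baseline together.

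That sentence governs the primary analysis: "The primary outcome will be change in CRQ dyspnea domain (CRQ-D) from baseline to end intervention". Under Sample size, the design aim is that "the 95% confidence interval will exclude a difference in means of 2.5 points or more". The calculation "assumes a standard deviation of the change in CRQ-D of 4.8 points" and makes no stated allowance for covariates.

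**The concern.** There are two separate weaknesses.

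1. **Design and model do not match.** Stratified allocation balances the arms on the three factors, so the treatment estimate already varies less between repetitions of the trial. A model without a prognostic stratification factor leaves that factor's variance in the residual. The standard error is then overstated and the interval covers more than 95% of the time. Equivalence requires the whole interval to lie inside ±2.5 points, so excess width costs power.

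2. **The covariate set is open.** With no rule for when adjustment is required, the analyst could in principle see both the adjusted and the unadjusted interval before choosing. In an equivalence trial, choosing the more favourable interval works in favour of the hoped-for conclusion.

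**Working it through.** **Inputs from the Sample size section:** margin 2.5 points, SD of change 4.8, true difference 0, 64 per group, 95% interval.

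**Inputs not in the documents (assumed):** the share of variance in change explained by baseline (R²b, 0 to 0.30) and by recruitment state and ILD jointly (R²s, 0 to 0.10).

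**The plan's own figure.** For equivalence with a true difference of 0, n per group = 2 × [SD × (z₁₋ₐ + z₀.₉₀) / margin]².
- With a 95% interval: 2 × [4.8 × (1.960 + 1.282) / 2.5]² = 77.5, so 78 per group, 156 in total.
- With a 90% interval: 2 × [4.8 × (1.645 + 1.282) / 2.5]² = 63.1, so 64 per group, 128 in total.

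The stated 128 therefore matches a 90% interval. Under the stated 95% interval, SE = 4.8 × √(2/64) = 0.849, half-width = 1.96 × 0.849 = 1.66, and power = 2Φ(2.5/0.849 − 1.96) − 1 = 67.6%. That mismatch is a separate matter. It matters here only because it leaves no spare precision.

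**Cost of leaving out the two factors, baseline adjusted for in both models.** Suppose stratification balances the factors perfectly. The estimate then has true SE = 4.8 × √(1 − R²b − R²s) × √(2/64) whether or not the factors are in the model. Only the half-width changes:
- factors omitted: 1.96 × 4.8 × √(1 − R²b) × √(2/64)
- factors included: 1.96 × 4.8 × √(1 − R²b − R²s) × √(2/64)
- power = 2Φ[(2.5 − half-width) / true SE] − 1

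| R²s, R²b | True SE | Half-width omitted → included | Power omitted → included |
|---|---|---|---|
| 0.05, 0.10 | 0.782 | 1.58 → 1.53 | 76.2% → 78.3% |
| 0.10, 0.20 | 0.710 | 1.49 → 1.39 | 84.6% → 88.2% |

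**Simulation of the same comparison.** 128 participants, three sites, half recruited after hospitalisation and one fifth with ILD (assumed shares), stratified blocks of four, t-based 95% intervals. Cells show half-width, then power.

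| R²s, R²b | Centre only | Centre + baseline | All strata + baseline | Gain from the two factors |
|---|---|---|---|---|
| 0, 0 | 1.68, 66.9% | 1.68, 65.8% | 1.69, 65.8% | 0 |
| 0.05, 0 | 1.68, 66.8% | 1.69, 65.9% | 1.64, 69.3% | 3.4 points |
| 0.10, 0 | 1.68, 67.9% | 1.68, 66.9% | 1.60, 71.9% | 5.0 points |
| 0.05, 0.10 | 1.68, 67.7% | 1.60, 74.5% | 1.56, 76.6% | 2.1 points |
| 0.10, 0.20 | 1.68, 68.6% | 1.51, 82.3% | 1.41, 86.9% | 4.6 points |
| 0.10, 0.30 | 1.68, 68.5% | 1.41, 88.9% | 1.31, 92.6% | 3.7 points |

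The two factors add about 2 to 5 points where they are prognostic and nothing where they are not. Where baseline is prognostic, it supplies most of the total gain.

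**Cost of the open choice.** The true difference is set at the margin (2.5 points), with 64 per group and 20,000 repetitions. Equivalence is declared if either the unadjusted or the baseline-adjusted 95% interval lies inside ±2.5.

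| R²b | Unadjusted | Adjusted | Either |
|---|---|---|---|
| 0.1 | 2.3% | 2.4% | 3.0% |
| 0.2 | 2.5% | 2.5% | 3.5% |
| 0.3 | 2.5% | 2.5% | 3.8% |

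Each prespecified analysis holds its level of about 2.5%. Only the selection between them exceeds it.

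**The case against.** The strongest reply is that a journal article condenses the protocol: one sentence cannot carry a full covariate list, an analysis plan not shown here may complete it, and nothing in the sentence rules out the other two factors. This stands in part, since the plan may well add them. But the article is not silent. It gives a covariate list, that list differs from the stratification list in the same article, and it is conditional.

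The qualifier also has an innocent reading. The sentence covers all continuous outcomes, and some, such as sessions attended or follow-up costs, have no baseline value to adjust for. *As required* may mean only *where applicable*. That is fair: the text permits a choice after seeing the data, but does not show that one is intended.

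Three stronger readings are tempting, and the documents do not support them.
- *The interval is needlessly wide, as a matter of fact.* No figure is given for the prognostic strength of recruitment state, ILD or baseline CRQ-D. At R² = 0 nothing is lost.
- *Full adjustment would recover most or all of the gap between 67.6% and 80% power.* Reaching 80% by formula needs a total R² of about 0.174 (residual SD 4.36 against 4.8). That calculation starts from a model with no covariates, whereas centre and baseline are already named. The change to the covariate list is the two omitted factors, worth a few points at most in these scenarios.
- *The completion analysis has the same fault.* There the proportion "will be compared between groups using a chi-squared test and the relative risk of non-completion will be determined". An unadjusted test is valid under this randomisation, and the hypothesis is that completion will be higher with telerehabilitation, so the width of an equivalence interval is not at issue. A stratified relative risk would be a preference.

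**Conclusion.** The point holds in a limited form. Read as written, the primary equivalence model names one of three stratification factors and does not commit to its covariates.

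The omission errs on the safe side: it can cost power but does not raise the risk of a false claim of equivalence. The 2–5 points of power rest on the assumed 5–10% of variance and on the simulated mix of participants.

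The conditional wording is the only part that touches error control. The 3.0–3.8% is what would follow if the more favourable result were always taken, so it measures what the wording allows and does not forecast what the investigators will do.

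Both effects are modest. The change is still worth making because the primary conclusion turns on interval width and the remedy needs no new data.

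**What to change.** Replace the model sentence with a statement that the primary CRQ-D model, and the model for every other continuous outcome measured at baseline, includes as fixed terms the baseline value of that outcome, recruitment state, recruitment site, and ILD versus other diagnoses. Delete the qualifier. For continuous outcomes without a baseline measurement, say that the three stratification factors alone are included.

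The cost is one or two sentences in the protocol or analysis plan. The variables are all recorded before allocation. Beyond centre and baseline, the model gains two parameters, and the price if neither factor is prognostic is negligible (simulated half-width 1.683 against 1.685). The article reports recruitment as continuing, so at that stage the change could be made and dated before any comparison of the arms. The completion analysis can stay as it is.

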#### Data integrity and management

Data will be stored on a purpose-built online database (www.adeptrs.com), with encryption, password protection and restricted access. No identifying information will be stored in the online database.

#### Withdrawal

A participant will be considered to have withdrawn from the study when consent is revoked. If this occurs, no further assessments will be performed. Participants will be informed that data collected up to the time of withdrawal will form part of the study results unless permission is expressly declined. Withdrawn participants will not be replaced. Protocol violations will not constitute grounds for withdrawal. Study withdrawal will not have any impact on care provided by any of the participating sites.

#### Monitoring

The trial will be monitored by an independent Data Safety Monitoring Board (DSMB) comprising a respiratory physician and two clinical research physiotherapists, with consultation with a statistician as required. The DSMB will review data relating to the primary outcome (CRQ-D) as well as 6MWD, endurance cycle time and Hospital Anxiety and Depression Scale scores. Data will be presented to the DSMB in a blinded fashion. The DSMB will initially review data at a time 6 months from the commencement of recruitment. Any serious adverse events will be notified immediately to the overseeing ethics committee (Alfred Health) and the relevant site governance committee, as well as to the DSMB. If there are concerns about the safety of participants, the DSMB will make a recommendation to the trial steering committee about continuing, stopping, or modifying the trial.

## Discussion

Pulmonary rehabilitation is a key recommended component of the non-pharmacological management of individuals with chronic respiratory disease [4], yet limited access to programs prevents the widespread application of its benefits. This study will compare both the clinical- and cost-effectiveness of delivering pulmonary rehabilitation via telerehabilitation, using readily available consumer devices and equipment, to a traditional centre-based program.

The telerehabilitation model under investigation directly addresses access barriers for both individual patients and the health system. By delivering pulmonary rehabilitation directly into the homes of people with chronic respiratory disease issues of transport, travel, their associated costs and weather could be negated [13, 62]. By improving ease of access, more individuals may have the opportunity to develop an informed and positive perception of the benefits of pulmonary rehabilitation. Reduced healthcare utilisation has also been reported following completion of pulmonary rehabilitation [63], and thus implementation of telerehabilitation programs has the potential to positively impact on healthcare expenditure.

Unlike previous studies [23–25, 27] the telerehabilitation model under investigation uses equipment that is familiar to clinicians and patients, requires little technical support, is scalable, and has the potential to be easily implemented into clinical practice. Telerehabilitation can be delivered any time and from any place, further extending access to patients who live away from metropolitan centres. By providing supervised exercise training in this way, pulmonary rehabilitation could be accessed in locations where specialist services would ordinarily be unavailable [64]. The remote supervision of exercise training in this telerehabilitation model is a key feature frequently unavailable in models of pulmonary rehabilitation not based in a healthcare setting. In a recent study of home-based pulmonary rehabilitation, 80% of individuals who did not wish to take part in the study declined because they wanted to attend the supervised pulmonary rehabilitation group [20]. By providing supervised exercise remotely, individuals who would otherwise be reluctant to exercise without the support of a healthcare professional may be more inclined to participate.

The purpose of this study conforms with policy statements to encourage the investigation of alternative models of pulmonary rehabilitation delivery in order to enhance implementation, access and delivery of pulmonary rehabilitation [15]. If this study demonstrates that telerehabilitation has equivalent clinical outcomes to centre-based pulmonary rehabilitation, and is cost-effective, this model has the potential to significantly increase service availability and accessibility through increased options for pulmonary rehabilitation delivery.

### Trial status

Recruitment commenced in August 2016 and is continuing.

## Abbreviations

6MWD: Six minute walk distance
BMI: Body mass index
COPD: Chronic obstructive pulmonary disease
CPET: Cardiopulmonary exercise test
CRQ: Chronic respiratory disease questionnaire
CRQ-D: Chronic respiratory disease questionnaire – dyspnea domain
DSMB: Data safety monitoring board
HRQoL: Health related quality of life
ILD: Interstitial lung disease
km/hour: kilometres per hour
MID: Minimal important difference
QALYs: Quality adjusted life years
SF-36v2: 36 item short-form health survey version 2
VO_2_: Oxygen uptake
